**Table 1 Tab1:** **Outcome measurements according to periods of follow-up and type of collection**

**Time**		**Outcome measurements**
Outcomes measured on patients		
M0, M3, M6, M12, M18, M24 (F to F)		Demographic data, health history, history of DM, DM health status, current medications, risk factors for complications of poorly controlled DM
*Laboratory measurements*		
M0, M12, M24 (CT)		HbA1c; fasting glucose; total cholesterol; HDL, LDL, and non-HDL cholesterol; triglycerides; serum creatinine; albumin/creatinine ratio; and glomerular filtration rate
M3, M18 (CT)		HbA1c, fasting glucose
M6 (CT)		HbA1c, fasting glucose, total cholesterol, HDL, LDL cholesterol, and triglycerides
*Anthropometric measurements*		
M0, M3, M6, M12, M18, M24 (F to F)		BMI, waist/hip ratio, systolic and diastolic blood pressure, heart rate
*Macro and microvascular complications*		
M0, M12, M24 (F to F, ECR)		Incidence of new ischemic heart events, hospitalization for congestive heart failure, peripheral artery disease, carotid stenosis fulfilling criteria for endarterectomy or confirmed ischemic or hemorrhagic stroke, incidence or progression of diabetic retinopathy, incidence or progression of diabetic nephropathy
*Eye examination*		
M3, M24 (CT)		Retinography and macular examination by OCT
*Instruments used for self-reported outcomes measures*		
M0, M12, M24	(SRI)	ADDQoL-19, BDI-II, DES-SF, DDS2, DIATEK, IPAQ, MEDAS, STAI-S, INDICA-LSQ
	(F to F)	EQ-5D-5 L, MMAS
M6, M18	(SRI)	ADDQoL-19, IPAQ, MEDAS
	(F to F)	EQ-5D-5 L, MMAS
*Healthcare utilization*		
M0, M3, M6, M12, M18, M24 (F to F, ECR)		Visits to primary care services, nurses, specialists; hospital admissions, emergency room visits, laboratory procedures, and other diagnostic tests; medication
*Satisfaction*		
M24 (SRI)		INDICA-SATP
Outcomes measured on physicians and nurses		
M0 (F to F)		Demographic data, years in practice, practice descriptors
M0, T3 (SRI)		INDICA-KNOW, LATCon
M24 (SRI)		INDICA-SATC

BMI: body mass index; F to F: face to face interview; CT: clinical test; DM: diabetes mellitus; ECR: electronic clinical records; HDL: high-density lipoprotein; LDL: low-density lipoprotein; OCT: optical coherence tomography; SRI: self-reported interview.

Note: see description of the questionnaires in Table 2.

#### Secondary endpoints

A broad set of secondary outcomes are measured (Table 1), including the following:*Cardiovascular risk factors*: mean change of BMI, waist circumference, and waist-to-hip ratio, systolic and diastolic blood pressure, total cholesterol and its fractions (low-density lipoprotein (LDL), high-density lipoprotein (HDL), and nonHDL), and triglycerides. Blood pressure is measured twice in one arm (right when possible) in a sitting position, with a digital sphygmomanometer trademark OMRON© model M6, and the average of the two readings will be recorded. Smoking status is determined by self-report of whether the subject currently smoked.*Macrovascular diabetes complications*: new ischemic heart events (angor pectoris, myocardial infarction, surgical or percutaneous coronary revascularization), hospitalization for congestive heart failure, peripheral artery disease (surgical or percutaneous peripheral arterial revascularization, nontraumatic lower limb amputation), carotid stenosis fulfilling criteria for endarterectomy, or confirmed ischemic or hemorrhagic stroke. The annual occurrence of cardiovascular events, surgical procedures, or hospitalization is verified by reviewing the medical records.*Microvascular diabetes complications*: Incidence and progression of diabetic nephropathy: mean change in UACR, UACR ≥ 30 mg/g, mean change in estimated glomerular filtration rate (eGFR), eGFR < 60 mL/min/1.73 m^2^ and need for renal replacement therapy (dialysis or renal transplantation). Incidence and progression of diabetic retinopathy, according to the results of a retinography, and incidence and progression of diabetic macular edema, according to the results of an optical coherence tomography (OCT) and a retinography, are measured at months 3 and 24 of the study. Incidence of diabetic polyneuropathy is measured using the Michigan Neuropathy Screening Instrument (MNSI), an emergent instrument used to assess distal diabetic peripheral polyneuropathy. Only the 15-item self-administered MNSI, which is scored by adding up abnormal responses [41] will be applied. MNSI was translated into and back-translated from Spanish for its use in the INDICA study.*Health-related quality of life* (*HRQoL*), *distress*, *anxiety*, *depression*, *satisfaction with the interventions*, *health behaviors*, *and changes in knowledge about diabetes self-management*: all instruments selected to measure these outcomes are reported in Table 2.

**Table 2 Tab2:** **Instruments used for self-reported outcomes measures**

**Instruments**	**Outcome measurements**
Outcomes measured on patients	
EQ-5D-5L [59]	Generic HRQoL questionnaire. The self-reported description assesses five domains: mobility, self-care, usual activity, pain/discomfort, and anxiety/depression
ADDQoL-19, Audit of Diabetes-Dependent Quality of life [60]	Specific HRQoL questionnaire for DM. It assesses 19 domains: leisure activities, working life, travel, holiday, physical activities, family life, social life, personal life, sex life, physical appearance, self-confidence, motivation, reaction from others, feelings about the future, financial situation, living conditions, reliance on others, freedom to eat, and freedom to drink
DDS2, Diabetes Distress Scale [61]	It is a validated two-item diabetes distress-screening instrument that asks respondents to rate on a six-point scale the degree of distress caused by the two following items: (1) feeling overwhelmed by the demands of living with diabetes and (2) feeling that I am often failing with my diabetes regimen
STAI-S, State Trait Anxiety Inventory [62]	It is a self-description questionnaire including two non-dependent scales, the applied state-anxiety scale (STAI State) and the trait-anxiety scale (STAI Trait). It assesses transient emotional state or condition as characterized by subjective feelings of tension and apprehension that can fluctuate in time and intensity
BDI-II, the Beck Depression Inventory II [63]	It is a validated 21-item self-report inventory that measures depressive symptoms such as sadness, pessimism, suicidal thoughts or wishes, tiredness or fatigue, loss of energy, and loss of pleasure, among others
DES-SF, Diabetes Empowerment Scale-Short Form [64]	This questionnaire assesses patient empowerment on T2DM management, including eight items with responses on a five-point Likert scale
IPAQ, International Physical Activity Questionnaire. [65]	This questionnaire checks physical activity and provides information on the time spent on walking, moderate-intensity activities, and vigorous and sedentary activities
MEDAS, Mediterranean Diet Adherence Screener [66]	This questionnaire assesses diet recommendation adherence. It consists of 14 targets for food consumption rated with one point for each target achieved
MMAS, Morisky Medication Adherence Scale [67]	This questionnaire assesses the medication adherence, including a four-item self-report measure with an established concurrent and predictive validity
INDICA-SATP	Patient satisfaction and usability of the web portal and the mobile phone communication system are assessed with a specific instrument created in the context of this project
Diatek	It is a specific instrument created in the context of this project, to assess potential changes in patient knowledge about DM based on the CPG INDICA
INDICA-LSQ	It is a specific instrument created in the context of this project used to assess attitudinal changes of patients regarding lifestyles, based in the Transtheoretic Model of Behavior Change [68]
Outcomes measured on physicians and nurses	
LATCon, Leeds Attitude toward Concordance scale [69]	It is a 12-item self-reported scale to assess patients’ and health professionals’ attitudes toward concordance in medicine-taking
INDICA-KNOW	Knowledge change among healthcare professionals will be measured with the aid of an instrument with 20 questions based on the contents of the INDICA CPG
INDICA-SATC	Acceptability and usability of the DST and the feedback screen is measured according to four different dimensions: acceptability of interactions and time devoted using the software communication technology, impact on patients, impact on the clinician’s practice, and communications issues such as quality of feedback and formats used [70]

DST: decision support tool.*Attitude toward concordance and knowledge about the clinical management of diabetes*: these instruments, reported in Table 2, are used to evaluate the interventions on physicians and nurses included in groups 2 and 3.

##### Healthcare utilization

Costs because of the clinical management of T2DM in all groups will be assessed from the healthcare services perspective, including the costs related to the development and use of all components for each intervention assessed (group sessions, ICT system, SMS services, computer-assisted aids, etc.). The analysis will also include costs because of patient contacts with primary care services, hospital admissions and length of stay, outpatient visits, emergency attendances, and prescribed medications. The volume of resource used for each cost component will be measured with the aid of patient questionnaires and ECR; unit costs will be taken from standard published sources when available and from the specific providers.

#### Measurement procedures

Information needed from patients are being collected by several procedures, including face-to-face interviews, clinical examinations, analysis of data stored in the ECR, downloading of information from the INDICA web platform, and self-completed questionnaires. Results of laboratory tests will be downloaded from ECR by trained staff blinded to patient group assignment.

Information needed from FCUs is being obtained by means of personal interviews and self-reported questionnaires.

The planning of information collection for every outcome measured throughout the project is shown in Table 1.

#### Biochemical determinations

Blood and urine samples are being collected after an overnight fast, by research nurses, using the available facilities of the participating PHCPs. After centrifugation, samples are being immediately transported to the biochemistry laboratory of the corresponding reference hospital. HbA1c is being quantified according to the Diabetes Control and Complications Trial assay. LDL cholesterol will be estimated using the Friedewald formula, and nonHDL cholesterol will be calculated as the difference between total cholesterol and HDL cholesterol. Estimated glomerular filtration rate will be calculated using the Modification of Diet of Renal Disease formula (MDRD4).

#### Biological samples for future research questions

To facilitate efficient answers to potential future research questions on T2DM in the Canarian population, urine and blood samples of patients are being frozen and stored. This will enable collating a collection of biological specimens from a wide and representative sample of the overall T2DM population in the Canary Islands. Urine and serum samples are being obtained at baseline and 24 months, while DNA samples are only being obtained at baseline. Every patient will be specifically informed and asked to consent to storage of DNA and nonDNA biological samples. These samples are being stored in the biobanks of the hospitals of the Canary Islands belonging to the Spanish National Biobanks Network. This process is in accordance with prevailing Spanish laws on protection of personal data [42], patient autonomy [43], and biomedical research [44]. These materials will subsequently be used to search for genetic or biological markers that could either characterize the T2DM patient population or predict clinical disease course.

#### Statistical methods

Generalized linear mixed models with repeated time measurements will be used to analyze changes in outcomes over time. To compare the three interventions and the control group after different follow-up periods (Baseline, 3, 6, 12, 18, and 24 months), the intervention groups will be treated as a ‘factor within.’ First, we will examine whether the intervention in Groups 1 and 2 are better than usual care, and then, we will examine whether the most intensive intervention (group 3) is better than less intensive interventions (groups 1 and 2). The purpose of these analyses is to obtain preliminary estimates regarding the incremental benefits of the intervention components [45]. For multiple comparisons, the *P* value will be adjusted with Bonferroni correction (Pc Z corrected value). In addition, the models will include a subset of covariates that are imbalanced at baseline. To identify the covariates to be included in the model, we will first fit separate models including each covariate, one at a time. The final model will include those covariates such that their inclusion changes the estimates’ treatment effect by at least 10%. As suggested in the CONSORT statement, decisions about covariates will not be based on *P* value [46,47].

To incorporate the effect of cluster analysis, a multilevel model (MLM) approach will be implemented. MLM adjusts for the clustering effects across three levels (patients, FCU, and PHCP) of the hierarchical data structure.

For the main intention-to-treat analysis comparing outcomes, all patients will be included. Standard imputation methods (i.e., mean value imputation, last observation carried forward) will be used to impute missing data depending on the pattern of missing data. All tests will be two-sided with a type I error of 5%. Statistical analyses will be performed using Statistical Package for social Sciences (SPSS v.21, Chicago, IL, USA).

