##### Sample size calculation

We estimated that 393 patients per arm (total in the study = 1,572) were needed to detect an absolute difference in Hba1c of 0.4%, assuming a common standard deviation of 1.4% [40], a two-tailed power of 90%, and an alpha of 0.05. After an additional adjustment for clustering of patients within FCU by the design effect [48], assuming 15 patients per FCU and an intra-class correlation coefficient of 0.01 (interquartile range: 0 to 0.032) based on data from the literature [49], the estimated number of patients per arm was 448 (total in the study = 1,792). Although the unit of allocation was the PHCPs, these are formed of several healthcare centers throughout the territory that only share administrative management and some services. Also, this effect was already controlled by means of the stratification. Therefore, we considered that the intra-class correlation within PHCP was insignificant, and we used instead the intra-class correlation for FCU, that is, among patients served by the same FCU. Although small, we consider that this correlation is significant.

However, sample size was increased by an additional 30% to accommodate for expected losses to follow-up and to warrant the presence of each arm in the study in the different islands. Hence, we aimed for a total sample size of 2,330.

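### Single-step Bonferroni gives up a modest amount of power that Holm's step-down procedure would keep at the same family-wise error rate

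*Protocol article*

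**What the plan says.** Statistical methods sets out the group comparisons in two steps. The first: "First, we will examine whether the intervention in Groups 1 and 2 are better than usual care". The second asks "whether the most intensive intervention (group 3) is better than less intensive interventions (groups 1 and 2"). Read pairwise, that is four contrasts: group 1 and group 2 each against usual care, and group 3 against each of groups 1 and 2. For multiple comparisons the P "value will be adjusted with Bonferroni correction". The section adds "All tests will be two-sided with a type I error of 5"%.

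It names no Holm, closed or gatekeeping procedure. The two steps give an order of examination, with no rule that passes alpha from one to the next. The number of comparisons in the family is not stated. The stated aim is estimation as well as testing: "The purpose of these analyses is to obtain preliminary estimates regarding the incremental benefits of the intervention components". The only confidence intervals mentioned are those for the incremental cost-effectiveness ratio, under Short-run model.

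Sample size calculation assumes "an absolute difference in Hba1c of 0.4"%, "assuming a common standard deviation of 1.4"%, and "a two-tailed power of 90%, and an alpha of 0.05". No multiplicity adjustment is stated there.

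**The concern.** Unqualified Bonferroni compares every P value with 0.05/m, where m is the number of comparisons, whatever the other P values show. Holm orders the P values and compares the smallest with 0.05/m, the next with 0.05/(m − 1), and so on, stopping at the first that fails. Its first step is the Bonferroni test and every later threshold is more lenient. It therefore cannot lose a rejection that Bonferroni makes, and it needs no assumption about the correlation between contrasts that share an arm.

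What is at stake is the second and later findings: whether the weaker of the two components, or the increment of the combination over a single component, is declared once another contrast already has been. Those are the questions that the second step of the analysis asks.

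**Working it through.** **Inputs** (Sample size calculation): difference 0.4; SD 1.4; 15 patients per Family Care Unit and intra-class correlation 0.01, so design effect 1 + 14 × 0.01 = 1.14; 448 per arm after clustering.

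**The plan's own figures.** 393 × 1.14 = 448.0, as stated, and 1,792 × 1.3 = 2,329.6, which rounds to the stated 2,330. The starting figure of 393 does not reproduce: 2 × (1.960 + 1.282)² × 1.4² / 0.4² = 257.4, so 258 per arm. That is a separate matter. Below, 448 per arm is taken as planned, and 258 is used only as a sensitivity case.

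**Bonferroni power per contrast, by formula.**
- Effective n per arm = 448/1.14 = 393.
- Standard error of a difference = √(2 × 1.96/393) = 0.0999.
- Standardised difference = 0.4/0.0999 = 4.005.
- Four contrasts: two-sided level 0.05/4 = 0.0125, critical value 2.498, power Φ(4.005 − 2.498) = 93.4%.
- Three contrasts: level 0.05/3, critical value 2.394, power Φ(4.005 − 2.394) = 94.6%.

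**Holm thresholds with four contrasts:** 0.0125, 0.0167, 0.025, 0.05, in order of increasing P value. Power depends on the joint distribution of the contrasts, so it was simulated: 400,000 sets of four independent normal arm means, each with variance 1.96/393, and both rules applied to the same contrasts.

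| Scenario | Bonferroni, per real contrast | Holm, per real contrast | All contrasts, Bonferroni / Holm |
|---|---|---|---|
| Four contrasts, all 0.4 (reductions 0, 0.4, 0.4, 0.8) | 93.4% | 97.6% | 78% / 92% |
| Four contrasts, group 3 adds nothing (0, 0.4, 0.4, 0.4) | 93.4% | 94.5% | not applicable |
| Three interventions vs usual care, each 0.4 | 94.6% | 97.3% | 87% / 94–95% |
| Four contrasts, all at an assumed 0.3 | 69% | 80% | 27% / 54% |
| Four contrasts, all 0.4, effective n 258 | 77% | 87% | 40% / 67% |

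**Error rate.** With no true differences and four contrasts, the chance of any rejection is 4.5% under both rules. With four contrasts and group 3 adding nothing, the chance of a false rejection is 2.4% with Bonferroni and 4.4% with Holm, both within 5%.

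**Dominance.** In no replicate of any scenario did Bonferroni reject where Holm did not. The chance of at least one rejection was the same under both rules in every scenario.

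**The case against.** The strongest case for leaving the text alone is that nothing in it is wrong. Bonferroni controls the family-wise error and errs on the safe side, and choosing between two valid procedures can look like preference. That it is an efficiency point stands. That it is mere preference does not: the article fixes a concrete rule, and another dominates it for rejection at the same error rate. For the same reason this is not a detail left open for a later analysis plan.

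Three further objections have substance.

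- **Size.** Large gains appear only with an effect below the planned 0.4 or with precision worse than planned. At the protocol's inputs the gain is about 1 to 4 points per contrast. The document does not say that all four contrasts are expected to be non-null together; it says only that the trial will examine whether group 3 is better. The four-real-contrasts scenario needs the two components to add perfectly, and it favours Holm.
- **Intervals.** A reader might infer that the power is given away for nothing. The documents do not support that. Single-step Bonferroni has simple simultaneous intervals that match its tests, and the stated aim is preliminary estimates. This counts for less here because the article plans no simultaneous intervals for group differences.
- **Family.** The article does not define the family, and it mentions several follow-up times. The size of the gain depends on that choice. The direction does not, since Holm can be applied to whichever comparisons Bonferroni would have covered.

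A reader might also infer that the planned analysis is invalid, or that it will miss real effects. Neither follows: the error rate is controlled, and some real effects may, not will, go undeclared.

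**Conclusion.** The point holds as a modest, inexpensive gain in efficiency, of low severity. With the four named contrasts as the family and the protocol's own inputs, Holm adds about 4 points of power per contrast if all four differences are real, and 14 points for declaring all four. It adds about 1 point per real contrast if group 3 brings nothing beyond groups 1 and 2, and nothing to the chance of a first rejection. The gain grows if the effect or the precision falls short of plan.

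The figures rest on a normal approximation, an effective 393 per arm, no correlation at practice level and no attrition beyond the planned allowance. The assumed 0.3 difference is illustrative and does not come from the document. That Holm never rejects less than Bonferroni, at the same family-wise level, depends on none of these.

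**What to change.** In Statistical methods, replace the reference to Bonferroni correction with Holm step-down adjusted P values, applied to the same family of comparisons at the same two-sided 5% level. The change amounts to a few words and a sort of the P values, and it touches neither the design nor data collection. The trial is described as ongoing, so the change can be made before the analysis.

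The cost lies in the intervals. Holm has no equally simple simultaneous confidence intervals. If intervals for group differences are reported beside the Holm P values, label them as unadjusted 95% or as Bonferroni-width. State that they may not always match the test decision: an unadjusted interval can exclude zero where Holm does not reject, and a Bonferroni-width interval can include zero where Holm does.

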### Setting and recruitment

PHCP were randomly recruited in four of the seven Canary Islands (Tenerife, Gran Canaria, Lanzarote, and La Palma). Tenerife and Gran Canaria are the main and most populated islands, providing 12 PHCP each (four from metropolitan areas, four from the south, and four from the north). La Palma and Lanzarote are less populated islands and provided four PHCP each. The Human Resources Department of the CIHS at every island supplied us with an updated list of publicly available physician/nurses for every selected PHCP. FCUs’ recruitment in PHCPs was supported by informative meetings preceded by meetings with local health authorities as well as with the directors of all selected PHCP on every island. In these meetings, a 60–80-min presentation describing the study objectives, planned time frame and tasks to be developed by healthcare professionals, expected resources utilization, and funding procedures were detailed.

After FCUs agreed and consented to participate, the electronic clinical records (ECR) of all potentially eligible patients in the selected FCU were screened to verify all inclusion and exclusion criteria. Once identified, patients received a phone call to explain the study objectives, informing that they might be eligible to participate and inviting them to an initial meeting in their respective PHCP. In this meeting, the study staff provided face-to-face extended information about the study, confirmed patient eligibility, and invited them to sign individual patient informed consent.

When a participant physician/nurse left their practice, they were excluded from the study and replaced by the new physician/nurse. In groups 2 and 3, the educational intervention was given to the new healthcare professionals on an individual level. Their corresponding patients were kept in the study without changes.

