### Random assignment

Randomization was applied at different levels in every island included in the trial. Three different strata or geographic areas were set in Tenerife and Gran Canaria (metropolitan, northern, and southern areas). Four PHCP were randomly allocated to every stratum. Each PHCP was assigned to one of the three interventions or control arms by block permutation. La Palma and Lanzarote were geographically divided into four zones with only one PHCP available in each zone. Each of these PHCP was randomly assigned to one of the study arms. In every island, all arms were equally distributed.

Six FCUs were randomly selected from all those consenting participants at each PHCP. From all patients fulfilling inclusion criteria and consenting to participate in each PHCP, 15 were randomly selected per FCU. Exceptionally, more than six FCUs or more than 15 patients per FCU were selected, in order to recruit 90 patients at every PHCP.

While PHCP randomization was performed using block permutation at three different levels, second (FCUs) and third (patients) stage randomizations were performed by simple generation from a list of random numbers. PHCP assignment to interventions or control group was performed by the data manager.

In order to prevent potential contamination among study interventions, all FCUs at every PHCP were allocated to the same study group.

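### The model names no term for the geographic blocks used in randomisation, and the covariate rule would hardly ever admit them, so reported standard errors may be too large

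*Protocol article*

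**What the plan says.** In the Protocol article, Setting and recruitment takes 12 PHCPs from each of Tenerife and Gran Canaria, four in each of three areas. On the rest it says: "La Palma and Lanzarote are less populated islands and provided four PHCP each".

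Random assignment treats the three areas on each main island as strata and says: "Each PHCP was assigned to one of the three interventions or control arms by block permutation". For the two smaller islands it says: "Each of these PHCP was randomly assigned to one of the study arms". It adds: "In every island, all arms were equally distributed".

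Statistical methods plans mixed models with repeated measurements and three levels: patient, Family Care Unit (FCU) and PHCP. It names no island, area, stratum or block term. On further terms it says: "In addition, the models will include a subset of covariates that are imbalanced at baseline". Candidates are tried one at a time and kept if they move the treatment estimate by at least 10%.

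Sample size calculation gives the stratification as one reason for treating correlation within PHCPs as insignificant: "Also, this effect was already controlled by means of the stratification".

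**The concern.** Stratified allocation makes the arm contrast more precise, because differences between areas cancel when every area contributes one PHCP to each arm. The estimated standard error reflects that gain only if the strata are in the model. Otherwise the differences between areas are counted as PHCP-to-PHCP noise within arms.

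The article counts on the gain when it sets the sample size, but the analysis it describes does not take it. It also fixes a selection rule that looks for imbalance, which the allocation was designed to prevent. At stake are the width of the confidence intervals and some power, in a trial with eight PHCPs per arm.

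**Working it through.** **Number of blocks.** This is derived; the article does not state it. The main islands give 2 × 3 areas = 6 sets of four PHCPs, and the smaller islands give 2 sets of four. So 6 + 2 = 8 blocks, 8 × 4 = 32 PHCPs and 8 per arm.

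**Can the covariate rule select the blocks?**
- *Imbalance condition.* Each block has one PHCP per arm, with a target of 90 patients in every PHCP. Blocks are therefore balanced in PHCPs and nearly so in patients.
- *10% condition.* With equal PHCP sizes, adding blocks changes the arm contrast by exactly zero. I simulated unequal sizes (50 to 90 per PHCP, SD 1.4, FCU ICC 0.01, PHCP ICC 0.01, all but SD and FCU ICC assumed) with a true difference of 0.4. Blocks met the 10% condition in about 2%, 3%, 7% and 16% of trials when they carried 0.005, 0.01, 0.02 and 0.05 of total variance.
- *Limit of this result.* The 10% is relative, so it is met more often when the effect is small: about 20% to 31% of trials at a true difference of 0.2 (block share 0.005 to 0.02), and 47% to 61% at zero. There it is the imbalance condition that keeps the blocks out.

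**Effect on the estimated variance.** Inputs:
- Patients analysed per PHCP: the article's 393 × (1 + 14 × 0.01) = 448 per arm, taking 393 as stated; 448 / 8 = 56.
- ICC: 0.01, 0.02 and 0.032. The article gives 0.01 and the upper quartile 0.032 for FCUs; 0.02 is an intermediate value. Using them for PHCPs is an assumption, since the article gives no PHCP value.
- Share *s* of PHCP variance lying between blocks: 1/4 or 1/2, assumed.

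In units of total variance, and ignoring the FCU level for simplicity, the variance of a PHCP mean is:
- blocks left out: ICC + (1 − ICC)/56
- blocks included: ICC(1 − s) + (1 − ICC)/56

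| ICC | Left out | Included, s = 1/4 | Ratio | Included, s = 1/2 | Ratio |
|---|---|---|---|---|---|
| 0.01 | 0.02768 | 0.02518 | 0.910 | 0.02268 | 0.819 |
| 0.02 | 0.03750 | 0.03250 | 0.867 | 0.02750 | 0.733 |
| 0.032 | 0.04929 | 0.04129 | 0.838 | 0.03329 | 0.675 |

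The estimated variance falls by 9%, 13% and 16% at s = 1/4, and by 18%, 27% and 32% at s = 1/2. Taking square roots, the standard error falls by 5% to 8% and by 10% to 18%.

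**Cost.** Cluster-level degrees of freedom go from 32 − 4 = 28 to 31 − 3 − 7 = 21, and the critical t from 2.05 to 2.08. If blocks do not differ, intervals widen by about 1.5%. Break-even is a variance ratio of (2.048/2.080)² ≈ 0.970. At ICC 0.01 that needs s ≈ 0.030 × 0.02768 / 0.01 ≈ 8%.

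**Power for a difference of 0.4 (SD 1.4, two-sided 0.05).** The true variance of the contrast is 1.96 × (2/8) × the *included* value in either analysis. With blocks I used the noncentral t on 21 df. Without them, the residual variance pools those 21 df with 7 block df whose expected mean square is larger by 4 × ICC × s.

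| ICC | s | Without blocks | With blocks |
|---|---|---|---|
| 0.01 | 1/4 | 0.92 | 0.93 |
| 0.01 | 1/2 | 0.93 | 0.95 |
| 0.032 | 1/2 | 0.74 | 0.85 |

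**Simulation check.** In the simulation above, block variance comes on top of a PHCP ICC of 0.01. With block shares of 0.005, 0.01 and 0.02, leaving blocks out gave type I error of about 0.031, 0.022 and 0.014 and power of 0.89, 0.86 and 0.80. Including them gave about 0.05 and 0.92. With no block variance, power was 0.93 without blocks and 0.92 with them.

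**The case against.** The omission is read partly from silence. An article need not list every model term, and the covariate rule can be read as covering patient characteristics only, with design factors left to the analysis plan. That is fair: one can say that the article names no block term, not that the final model will lack one. But the article does fix a rule for adding terms, makes no exception for design factors, and elsewhere relies on the stratification. That goes beyond a detail left open.

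The size is also open to challenge. No between-block variance is documented, the ICCs come from another level, and the primary endpoint is change from baseline, which removes stable differences between areas. All of this stands, and the true share may be small.

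A reader might infer three stronger things:
- *That the results would be biased or give false positives.* They would not. The estimate is essentially the same either way, and the error runs in the conservative direction.
- *That adding blocks makes the estimate itself more precise.* Randomisation has already done that. The model term only lets the reported standard error show it.
- *That island also separates the hospital laboratories measuring HbA1c, which makes block differences likely.* The article says samples go to the corresponding reference hospital, but not that laboratories match islands. A stable laboratory offset would in any case cancel in the change from baseline.

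**Conclusion.** The point holds as a conditional loss of efficiency. The allocation is blocked, the sample size section relies on that, and the analysis described neither names the blocks nor has a rule likely to bring them in. If HbA1c change varies between blocks, reported standard errors are too large and tests conservative. If it does not, nothing is lost.

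Under the assumptions above, the overstatement is such that including blocks lowers the estimated variance of an arm contrast by about 9% to 32%. At ICC 0.01 the gain in power is one to two percentage points. A gain of about eleven points needs the upper ICC and the larger block share together. The document does not support a flat statement that the intervals are too wide. The change is still worth making, because it costs little and brings the analysis into line with the design.

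**What to change.** State that the randomisation blocks (the three areas within each of Tenerife and Gran Canaria, plus La Palma and Lanzarote) enter the primary and secondary models as prespecified fixed effects, whatever their baseline balance or effect on the estimate. Limit the imbalance and 10% rule to other covariates.

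This is a change of wording and needs no new data. It uses 7 of the 28 cluster-level degrees of freedom (critical t 2.05 to 2.08).
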